## Abstract

**Background:**

People with cardiac disease and type 2 diabetes have higher hospital readmission rates (22%) compared to those without diabetes (6%). Self-management is an effective approach to achieve better health outcomes; however there is a lack of specifically designed programs for patients with these dual conditions. This project aims to extend the development and pilot test of a Cardiac-Diabetes Self-Management Program incorporating user-friendly technologies and the preparation of lay personnel to provide follow-up support.

**Methods/Design:**

A randomised controlled trial will be used to explore the feasibility and acceptability of the Cardiac-Diabetes Self-Management Program incorporating DVD case studies and trained peers to provide follow-up support by telephone and text-messaging. A total of 30 cardiac patients with type 2 diabetes will be randomised, either to the usual care group, or to the intervention group. Participants in the intervention group will received the Cardiac-Diabetes Self-Management Program in addition to their usual care. The intervention consists of three face-to-face sessions as well as telephone and text-messaging follow up. The face-to-face sessions will be provided by a trained Research Nurse, commencing in the Coronary Care Unit, and continuing after discharge by trained peers. Peers will follow up patients for up to one month after discharge using text messages and telephone support. Data collection will be conducted at baseline (Time 1) and at one month (Time 2). The primary outcomes include self-efficacy, self-care behaviour and knowledge, measured by well established reliable tools.

**Discussion:**

This paper presents the study protocol of a randomised controlled trial to pilot evaluates a Cardiac-Diabetes Self-Management program, and the feasibility of incorporating peers in the follow-ups. Results of this study will provide directions for using such mode in delivering a self-management program for patients with both cardiac condition and diabetes. Furthermore, it will provide valuable information of refinement of the intervention program.

**Trial Registration Number:**

ACTRN12611000086965

## Background

Cardiac disease and diabetes are the most prevalent chronic diseases in the Australian population. The number of people with diabetes is estimated to increase from 171 million in 2000 to 366 million by 2030 [1,2]. The prevalence of diabetes for Australians aged 25 or over in 1999-2000 was 7.4% (more than 1 in 14 people) and the average age of people with diabetes is getting younger [3]. In 2000-2003, it is reported that 6.6% of Australians aged 18 years and over had diabetes [3]. Australia's Health 2008 confirmed people diagnosed with type 2 diabetes are more vulnerable to cardiovascular complications, and are at greater risk of further cardiac events, leading to poor health-related quality of life [3]. People with diabetes were reported to rate their health three times lower than those without diabetes [3,4]. The direct costs of treating type 2 diabetes and its related complications is estimated to reach between $213-396 billion a year globally by 2025, which is as high as 40 percent of some countries' health care budgets [5-9]. Therefore, reducing the risk of diabetes and its associated cardiac complications is vitally important not only from a personal, but also an economic perspective.

Two previous studies undertaken by the first two authors provided the basis for developing the initial Cardiac-Diabetes Self-Management Program (CDSMP). An exploratory study of the demographic characteristics and incidence of critical cardiac admission for patients with type 2 diabetes over a four-year period indicated 15% of all Coronary Care Unit (CCU) patients had a previous diagnosis of type 2 diabetes, and 22% of these patients were readmitted to hospital within 28 days compared to only 6% of CCU patients without diabetes [10]. A second study using a qualitative interpretative approach to gain in-depth understanding of the needs and experiences of this at-risk group of patients, found four main themes of confidence in self, confidence in health professionals, feelings of hopelessness and fatigue were related to managing their conditions following discharge [11]. These findings highlighted the complexity for patients with these two conditions in undertaking self-management. Both studies were invaluable in the development of a new self-management program, the CDSMP, which was based on self-efficacy construct [12].

The self-efficacy construct is based on the effect of a person's belief in their abilities to successfully follow through with planned actions and accomplish goals. Furthermore, a person with high self-efficacy will tend to set higher personal goals than someone with low self-efficacy, who will have very little faith in his/ her ability to achieve in the area in question [13].

Current literature supports the success of self-management programs based on improving self-efficacy levels in modifying lifestyles for different patient groups with chronic diseases such as type 2 diabetes [14,15] and cardiac disease [16]. Patients with type 2 diabetes who are admitted to CCU following a critical cardiac event are suddenly confronted with a number of life style rules and advice in order to deal with their illnesses. Often these rules and recommendations are presented separately for each disease and not tailored to the needs of patients with both diabetes and a cardiac condition. Furthermore, such guidance is given by professionals who might not have experienced any of the challenges these patients now face.

Having peer support during this initial period is very valuable. A recent World Health Organisation (WHO) consultation on peer support programs indicated these were promising and presented recommendations for developing and evaluating such programs [17]. A peer support person is someone who has experienced similar conditions, been successful in managing their conditions and is able to provide relevant and meaningful information [18].

Although the benefits of peer support for improving chronic illness self-management, including diabetes, to achieve better health outcomes has been demonstrated [18-22] there is limited evidence that self-management programs provided by or incorporating peers have improved psychological, or reduced health care utilization [22,23]. Furthermore, no research has yet been undertaken to evaluate the effectiveness of peer support for patients with both type 2 diabetes and cardiac conditions, nor has it been evaluated in different contexts (hospital and community).

## Aim

To develop and pilot test a Cardiac-Diabetes Self-Management Program (CDSMP) utilising peer support for improving self-management for patients with both diabetes and cardiac conditions.

### Objectives

• To further develop a CDSMP for patients with type 2 diabetes following a critical cardiac event, including the development of a DVD incorporating stories from a range of case studies, and use of former patients (peers) to provide support in adopting self-management strategies.

• To evaluate the feasibility and applicability of the DVD and peer supported CDSMP.

### Hypotheses

• Anticipated outcomes for the intervention group when compared to the control group receiving usual care will include:

• Higher self-management practice scores;

• Higher self-efficacy levels;

• Higher knowledge scores.

## Methods/Design

The pilot study using randomised controlled trial design (parallel-group trial) within the participants' usual health care environment will be conducted in three distinct but overlapping phases: (1) development of the training package including the CDSMP materials and Digital Video Disk (DVD), (2) peer selection and training, and (3) intervention phase. These will each be described below.

### Phase 1: Development of the CDSMP

The intervention utilised in this project will be based on the Cardiac Diabetes Self Management Program developed in earlier research by the first two authors [12]. It will be modified according to feedback from its initial trial, which included suggestions for adding a multimedia component; this will take the form of a DVD. The DVD will be provided to participants in the intervention group to assist them to apply strategies from the self-efficacy model; it will take the form of narrative "real-life" stories of people managing both diabetes and cardiac conditions. A further addition to the program will be the use of peers to provide follow-up support to participants.

The CDSMP program consists of three face-to-face sessions and telephone and text-messaging follow-up. The face-to-face sessions will be provided by a trained Research Nurse, and be conducted while the patients are in CCU and continue as the patient makes the transition home after discharge. The participants will be telephoned 1 week after discharge home and 2 text-messages will be sent a week after telephone follow up. These will be conducted by the trained 'peers'.

#### Reference Group

A reference group will be formed for the purposes of informing and reviewing program materials. The panel will consist of experts in the field (e.g. cardiologists, diabetes educators, cardiac rehabilitation coordinators) plus the researchers. After agreeing to participate, panellists will attend face-to-face meetings to establish the roles and responsibilities of the panel, such as reviewing and commenting on program development, including DVD production, and to agree on acceptable methods of communication. The panel will provide an important source of guidance in the production of all educational materials, in particular the DVD.

#### DVD Production

"Actors" in the DVD will be actual people dealing with diabetes and cardiac conditions and discussions will be held between these actors, the production team and Chief Investigator to ensure understanding of individual roles, as well as the DVD as a whole. Prior to production, reference group members will be given the opportunity to review and comment on the DVD script. The resulting DVD will be presented to the reference group for final approval before its use within the CDSMP.

### Phase 2: Peer Selection & Training

Selection and training of peer supporters is a crucial component to this project; a peer supporter is someone who has similar conditions, and can use their own experience to provide information to others. The peer support person can be very useful to others who are trying to work out the best ways of managing their health [18]. Potential peers, who are considered competent in the management of their conditions will be identified by the cardiologist and subsequently trained by the researchers. To facilitate the training process, a detailed peer training manual will be developed, also utilising self-efficacy principles.

### Phase 3: Intervention

Control group (group 1): Participants will receive usual care, which consists of education provided in the CCU and referral as necessary to the diabetes educator.

Intervention group (group 2): Participants will receive usual care and a combination of CDSMP sessions in the CCU, plus peer telephone and text follow-ups.

The CDSMP is designed to be administered on a one-to-one basis and to commence in CCU by staff members, then be followed up by trained peers via a telephone call one week after discharge and text message reminders from peers in weeks three and four. If a patient is transferred to a ward before completing the program, the hospital-based section of the CDSMP will be continued on the ward by the trained research nurse.

As part of the program, the DVD based on incorporating stories from a range of case studies is developed and will be provided to participants in the intervention group to assist them with the application of strategies from the Self-Efficacy Model.

#### Settings and locations

The study will be conducted in the Coronary Care Units (CCU) at Mater Health Services, and followed up by telephone and text messages at participants' homes in Brisbane, Australia.

## Participants

### Sample size

A total of 30 patients for 2 groups will be required. This sample size of 10-15 per group is suggested by Hertzog (2008) [19]. This number is calculated with an alpha of 0.05 and power of 0.9, thus 10 patients per group will be required to detect any statistical differences. Allowing 20% attrition rate, 13 patients per group will be required. Thus with an alpha of 0.05 and power of 0.9, 8 patients per group was required to detect any statistical differences.

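### The sample-size paragraph requires 10 and then 8 patients per group for the same alpha, power and target, and claims 90% power for any difference, which no fixed sample has

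*Protocol article*

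**What the plan says.** All of this stands in the Sample size section of the protocol article, in this order:

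- The total: "A total of 30 patients for 2 groups will be required".
- A rule of thumb from a cited source on pilot samples: "This sample size of 10-15 per group is suggested by" that source.
- A power calculation: "This number is calculated with an alpha of 0.05 and power of 0.9", and "thus 10 patients per group will be required to detect any statistical differences".
- Attrition: "Allowing 20% attrition rate, 13 patients per group will be required".
- A closing statement: "Thus with an alpha of 0.05 and power of 0.9, 8 patients per group was required to detect any statistical differences".

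No effect size, SD, outcome or sidedness is attached to the 10 or to the 8. The Data Collection section names three primary outcomes (self-efficacy, self-care behaviour, knowledge). The Data Analysis section plans a Mann-Whitney U test for the time-by-group comparison, with significance at p < 0.05. The Hypotheses section expects higher scores in the intervention group on all three outcomes.

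**The concern.** Two statements are wrong as written. First, the required number per group is given as 10 and as 8 under identical conditions. The 8 is presented as a conclusion, yet nothing before it leads there. Second, the power of 0.9 is claimed without limit on the size of the difference. Power is always power against a stated difference, and as the difference shrinks towards zero it falls to the significance level.

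The claim has some weight even in a pilot, because directional hypotheses are to be tested at p < 0.05. A reader who accepts 90% power could take a non-significant result on self-efficacy, self-care or knowledge as evidence that the program does not work. The Limitations section also says that the pilot will guide the power analysis of a larger study, so its own power should be described correctly.

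**Working it through.** **Inputs from the article.** Alpha 0.05; power 0.9; 10 and 8 per group; 20% attrition; 13 per group; 30 in total (Sample size). Mann-Whitney U as the between-group test (Data Analysis). Simple randomisation (Randomisation).

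**Assumptions, because the article is silent.** Two-sided testing, normal data, about equal groups, and standardised differences d (difference divided by SD) of 0.5 and 0.8 as reference points.

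**1. Attrition step.** n/(1 - 0.20): 10/0.8 = 12.5, rounded up to 13. This reproduces the article's 13, so the 13 is built on the 10. From 8 the same step gives 8/0.8 = 10, not 13.

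**2. The 10 and the 8.** Neither can be reproduced without an effect size, so I solved for the difference each implies. The normal approximation is d = (1.960 + 1.282) x sqrt(2/n):

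- n = 8: 3.242 x 0.500 = 1.62
- n = 10: 3.242 x 0.447 = 1.45

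The exact t calculation is more accurate at these sizes. The Mann-Whitney values come from simulation with exact critical values.

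| Per group | d for 90% power, t-test | d for 90% power, Mann-Whitney |
|---|---|---|
| 8 | 1.745 | about 1.80 |
| 10 | 1.534 | about 1.62 |
| 12 | 1.385 | about 1.45 |
| 15 | 1.226 | about 1.28 |

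The 8 and the 10 therefore correspond to different target differences. Under one set of assumptions they cannot both be the required number.

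**3. Power at moderate differences** (simulated Mann-Whitney, two-sided, 6,000 runs per cell).

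| Per group | d = 0.5 | d = 0.8 |
|---|---|---|
| 8 | 15% | 30% |
| 10 | 16% | 36% |
| 12 | 19% | 43% |
| 15 | 23% | 52% |

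The row for 12 is the one to expect: 15 x 0.8 = 12 completers. A one-sided t-test with all 15 per group retained still gives only 38% at d = 0.5 and 69% at d = 0.8. For 90% power by two-sided t-test, 86 per group would be needed at d = 0.5 (85.03 rounded up) and 34 at d = 0.8 (33.83 rounded up).

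**4. The total.** 2 x 13 = 26, which 30 covers. 30/2 = 15 is the top of the cited 10-15 range.

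**5. Precision with 12 completers per group.** The 95% CI half-width for a mean difference is t(0.975, 22) x sqrt(2/12) = 2.074 x 0.408 = 0.85 SD.

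**6. Unequal groups.** The allocation ratio is not stated. At 1:1, simple randomisation of 30 gives exactly 15/15 with probability C(30,15)/2^30 = 0.14, and a split of 12/18 or worse with probability about 0.36. A 12/18 split less 20% leaves about 10 and 14 completers. The half-width is then 2.074 x sqrt(1/10 + 1/14) = 2.074 x 0.414 = 0.86 SD, slightly worse.

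**The case against.** The strongest defence is that this is a pilot. The number randomised rests on the cited 10-15 per group range and depends on neither the 10 nor the 8. No patients need to be added and no analysis changes. That stands, and it limits the consequence to what the paragraph claims. It does not remove the contradiction, and the power claim is not idle beside directional hypotheses tested at p < 0.05.

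A second defence is that this is a journal article, which may leave the effect size and SD to a fuller document, and that the word *any* may be loose English. The first part stands: a missing effect size alone would be no finding. But the article goes further and makes a positive claim that is false as worded.

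Third, the differences above are between-group. The Data Analysis section also plans within-group Wilcoxon tests. For a paired t-test the 90% thresholds are 1.34 SD of change at 8 and 1.15 at 10. These are lower, but still nowhere near any difference.

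Three stronger readings are tempting and not supported:

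- A reader might infer that 30 contradicts 26. The article never says that 30 is twice 13, and 30 exceeds what the attrition step asks for.
- A reader might infer that the detectable effects are implausibly large. The article gives no SD or expected effect for any outcome, so plausibility cannot be judged from it.
- A reader might infer that two calculations were merged. The 8 could come from one-sided testing (at d = 1.53, exact t gives 10.04 two-sided and 8.09 one-sided) or from 10 x 0.8 = 8. The text states neither.

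That null results will be misread is a risk; the article does not say it will read them that way.

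**Conclusion.** The point holds in two parts. The 10-versus-8 contradiction rests on the text alone and needs no assumption. It is not a matter of rounding, since each figure is given as the requirement and the 13 depends on one of them. That the unqualified 90% power claim is false also needs no assumption. Its size does: given two-sided alpha 0.05, normal data and near-equal groups, 90% power with the planned Mann-Whitney test starts at about 1.3 SD with all 15 per group and at about 1.8 SD with 8. With the expected 12 completers per group it starts at about 1.45 SD, and power at half an SD is about one in five. The paragraph must be corrected. The total of 30 may stay as a pilot size.

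**What to change.** Delete both power sentences, and with them the 13 that is built on the 10. In their place, state:

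- 30 patients will be randomised, about 15 per group (not exactly 15, because randomisation is simple), chosen as a pilot size within the cited range.
- With 20% attrition, about 12 per group are expected to complete.
- This gives a 95% CI half-width of about 0.85 SD for a between-group mean difference, 90% power by Mann-Whitney only for differences of about 1.45 SD or more, and about 20% power at 0.5 SD; all are slightly worse if the groups are unequal.
- A non-significant result will not be read as no effect.

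The half-width refers to a difference in means, while the planned tests are rank-based, so it should be labelled as a guide to precision.

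The cost is one reworded paragraph, with no extra patients and no change of design or analysis. The downside is that the stated power becomes less favourable.

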#### Inclusion criteria

Participants who will be included:

• are males and females aged over 18 years who have given their consent to participate in the study

• have had type 2 diabetes for at least one year and have been admitted to the CCU with a critical cardiac event in the study hospitals

• can read and converse in English

• are physically stabilised

• have a mobile phone

#### Exclusion criteria

• Potential participants will be excluded if they:

• are unable to read and speak English

• are transferred to another hospital.

• are on respiratory ventilation

• are unconscious

Minority groups or people from non-English speaking backgrounds (NESB) will be included unless they cannot read and speak English. English is needed, as the materials are in English. Programs for non-English speaking patients will be developed in future projects.

### Randomisation

Simple randomisation using a randomisation table (computerised sequence generation) will be used. Allocation will be concealed by using sealed, numbered, opaque envelopes to both control and intervention groups.

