### Procedure

The nominated RA will liaise with the Nurse Unit Manager (NUM) of the CCU, to obtain a list of eligible participants from the CCU Admission Book. The RA will then approach the potential participants for their informed consent and to collect baseline data. After baseline data is collected, a computer-generated list of random numbers produced by the researcher will then be used to randomly assign participants to either the control group or the intervention group (See Figure 1: Overview of data collection). Patients are blinded to receive either usual care or usual care and CDSMP, however the RA who assisting with data analysis is not blinded.

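### Simple randomisation of 30 patients leaves arm sizes to chance and misses the plan's 13 per group in about 36% of sequences; permuted blocks would be a cheap improvement

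*Protocol article*

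**What the plan says.** All references are to the protocol article.

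- Sample size, total and range: "A total of 30 patients for 2 groups will be required", with the remark that "This sample size of 10-15 per group is suggested".
- Sample size, basis: "This number is calculated with an alpha of 0.05 and power of 0.9, thus 10 patients per group will be required". No effect size, standard deviation or sidedness is given.
- Sample size, attrition: "Allowing 20% attrition rate, 13 patients per group will be required". The same paragraph ends with a smaller figure at the same alpha and power: "8 patients per group was required to detect any statistical differences".
- Randomisation, method: "Simple randomisation using a randomisation table (computerised sequence generation) will be used". No allocation ratio, block or cap on arm size is stated.
- Randomisation, concealment: "Allocation will be concealed by using sealed, numbered, opaque envelopes to both control and intervention groups".
- Procedure: once baseline data are in, "a computer-generated list of random numbers produced by the researcher will then be used to randomly assign participants". Envelopes are not mentioned there.

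**The concern.** The sample size is set per group, but the chosen randomisation fixes only the total. With 30 patients, chance imbalance is often large relative to the margin the plan allows itself: 15 per arm if the split is even, against 13 needed.

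What is at stake is information. Under Limitations, the pilot is meant to show feasibility and acceptability and to guide the power analysis of a larger study. If one arm is thin, there are few patients from whom to judge the programme's delivery (if it is the intervention arm) or the variability under usual care (if it is the control arm).

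A smaller matter is that the Procedure section describes assignment from a list without repeating the envelope step, so a reader cannot tell from that section how list and envelopes fit together.

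**Working it through.** **Inputs.** From Sample size: 30 in total, 10 per group completing, 20% attrition, 13 per group at entry. From Randomisation: simple allocation. Assumed: probability 1/2 per arm (no ratio is stated), and independent dropout with probability 0.20 per patient.

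**Step 1: reproduce the plan's figure.** 10 / (1 − 0.20) = 12.5, rounded up to 13. This matches. The underlying 10 (or 8) per group cannot be reproduced without an effect size.

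**Step 2: arm sizes at entry.** The size X of one arm follows Binomial(30, 0.5), and the smaller arm is below m with probability 2 × P(X ≤ m − 1), for m up to 15.

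| Event | Probability |
|---|---|
| Exactly 15:15 | 14.4% |
| An arm below 13 | 2 × P(X ≤ 12) = 36.2% |
| An arm below 12 | 20.0% |
| An arm below 10 | 2 × P(X ≤ 9) = 4.3% |
| An arm below 8 | 2 × P(X ≤ 7) = 0.5% |

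**Step 3: completers.** Given n₁ and n₂ = 30 − n₁ randomised, completers are Binomial(n₁, 0.8) and Binomial(n₂, 0.8). The chance that some arm has fewer than 10 is 1 − P(C₁ ≥ 10) × P(C₂ ≥ 10).

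- Fixed 15:15: P(C ≥ 10) = 0.939 per arm, so 1 − 0.939² = 11.8%.
- Fixed 14:16: 15.3%.
- Simple randomisation, averaging over n₁ with weights C(30, n₁)/2³⁰: 35.0%.

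**Step 4: power.** For a two-sided t-test at alpha 0.05 and power 0.9, 10 per group implies a standardised difference of about 1.53. This is a working assumption, since the article gives no effect size and plans rank tests. With no dropout, power at that effect is 98.2% at 15:15, 98.0% at 13:17, 97.8% at 12:18 and 96.9% at 10:20. With 20% removed from each arm, it is 94.8% at 15:15 (12:12 left), 94.0% at 12:18 (9.6:14.4 left) and 92.3% at 10:20 (8:16 left). With random 20% dropout, mean power is 93.4% under simple randomisation and 94.3% at 15:15. The chance that the patients who remain give less than 90% power is about 12% against 6%.

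**Step 5: effect of blocking.** Blocks of 2 or 6 throughout divide 30 exactly and give 15:15. Blocks of 4 leave two patients over, so the worst split is 14:16. With mixed sizes of 2, 4 and 6, the last block may be cut after an even number of patients, and the imbalance is then at most 2, again 14:16. The chance of an arm below 13 goes from 36.2% to 0, and the chance of fewer than 10 completers in some arm goes from 35.0% to between 11.8% and 15.3%.

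**The case against.** The strongest reply is that simple randomisation is a legitimate, openly stated choice, and that 13 per arm is not a true floor. It is 10 inflated for dropout, and a 12:18 split misses it at almost no cost in power because the larger arm compensates. The same section also gives 8 per group, and measured against 10 or 8 as numbers randomised, the shortfall is rare (4.3% and 0.5%). A feasibility pilot can tolerate some imbalance, and simple randomisation leaves nothing to guess, which counts in a trial where staff cannot be blinded.

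Most of this stands. The method is not an error, and how often the targets are missed depends on which figure is meant. But 13 per group is the figure the article itself derives for entry, and a smaller number elsewhere in the paragraph does not withdraw it. The reply about power also leaves the completer shortfall untouched.

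Two stronger readings are tempting, and the document supports neither. A reader might infer that unequal arms take power below the 90% on which the size was based. On average they do not: the planned 30 exceed the 2 × 13 = 26 required, and mean power stays above 93% at the implied effect. A reader might also infer from the Procedure section that assignment is made from an open list, in conflict with the envelopes. Nothing there says that the list is open or available to recruiters. The Randomisation section states that allocation is concealed, and a list that generates the sequence and envelopes that conceal it are two parts of one ordinary process.

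**Conclusion.** The point holds as a cheap design improvement. Under the stated method, one arm falls short of the article's 13 per group in 36% of sequences, and some arm has fewer than 10 completers in 35% of trials, against 12% at 15:15. The first figure assumes equal allocation probability; the second also assumes independent 20% dropout. The mean power cost is about one percentage point, at an effect size inferred from 10 per group. The consequence is missed per-group targets and a possible thin arm in a pilot that is to inform a larger trial. There is no bias and no material loss of power.

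On assignment, the two sections are compatible, and only a clarification of wording is warranted.

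**What to change.** In the Randomisation section, replace simple randomisation with 1:1 permuted blocks of randomly varying size (for example 2, 4 and 6), and state that block sizes are withheld from recruiting staff. In the Procedure section, add that the computer-generated list is used only to prepare the sealed, numbered envelopes. The existing order, with assignment after baseline data, can stay as it is.

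The cost is a new computer-generated list and two sentences. The downside is slight predictability near the end of a block, because staff will know past assignments; varying block sizes and the sealed envelopes already planned limit it.
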